## Abstract

**Background:**

People aged 75 years and over account for 1 in 4 of all hospital admissions. There has been increasing recognition of problems in the care of older people, particularly in hospitals. Evidence suggests that older people judge the care they receive in terms of kindness, empathy, compassion, respectful communication and being seen as a person not just a patient. These are aspects of care to which we refer when we use the term ‘relational care’. Healthcare assistants deliver an increasing proportion of direct care to older people, yet their training needs are often overlooked.

**Methods/Design:**

This study will determine the acceptability and feasibility of a cluster randomised controlled trial of ‘Older People’s Shoes’ a 2-day training intervention for healthcare assistants caring for older people in hospital. Within this pilot, 2-arm, parallel, cluster randomised controlled trial, healthcare assistants within acute hospital wards are randomised to either the 2-day training intervention or training as usual. Registered nurses deliver ‘Older People’s Shoes’ over 2 days, approximately 1 week apart. It contains three components: experiential learning about ageing, exploration of older people’s stories, and customer care. Outcomes will be measured at the level of patient (experience of emotional care and quality of life during their hospital stay), healthcare assistant (empathy and attitudes towards older people), and ward (quality of staff/patient interaction). Semi-structured interviews of a purposive sample of healthcare assistants receiving the intervention, and all trainers delivering the intervention, will be undertaken to gain insights into the experiences of both the intervention and the trial, and its perceived impact on practice.

**Discussion:**

Few training interventions for care staff have been rigorously tested using randomised designs. This study will establish the viability of a definitive cluster randomised controlled trial of a new training intervention to improve the relational care proided by healthcare assistants working with older people in hospital.

**Trial registration:**

The study was registered as an International Standard Randomised Controlled Trial (ISRCTN10385799) on 29 December 2014.

## Background

Older people account for a large and increasing proportion of those receiving National Health Service (NHS) acute care. In England in 2013, people over the age of 75 years accounted for 24 % of all hospital admissions, an increase of 57 % over the previous decade with the average hospital stay for this age group decreasing from 15.2 to 9.4 days [1]. The quality of care delivered to older people has come under increased scrutiny: a report by The King’s Fund cites 32 initiatives from statutory bodies, charities and campaign groups drawing attention to deficiencies in their care [2]. The King’s Fund’s Point of Care Programme was a response to a more general concern about ‘not getting the basics right’ in the delivery of care for older people [3, 4].

Just under a fifth of respondents to the NHS Inpatient Survey did not feel that they were treated with respect and dignity at all times [5] and in complaints received about NHS care, the second highest area of concern related to the attitudes of staff [6]. Recently, the Care Quality Commission (CQC) review of services in 2012 found that they were ‘struggling in areas such as dignity and respect, nutrition, care and welfare’ [7] and the Patients Association published 13 cases of care failures [8]. The Prime Minister has acknowledged this situation by prioritising the improvement of care standards in 2013 [9].

While patient-centred care is an explicit priority, there is a lack of clarity among staff at all levels as to what this actually means and how it can be practically implemented [10]. Emotional support, empathy and respect are the aspects of care considered most important by patients [11]. Key elements of dignified care include respectful communication, respecting privacy, promoting autonomy, addressing basic needs in a sensitive manner, and promoting a sense of identity [4]. Qualitative data from a study of older patients with acute care needs has highlighted the importance of timeliness of care (particularly around toileting needs) and interest in the person, kindness, compassion and attending to ‘the little things’ [12].

The focus of the proposed study is the relational care provided to older people in hospital. Relational aspects of care include dignity, empathy and emotional support as distinct from functional or transactional aspects of care [13]. In a review of studies of older people and their relatives’ experiences of acute care settings, it was the relational aspects of care that affected whether care experiences were perceived as good or bad [14]. Three themes that underscored older people’s understanding of relational care were identified in this review: older people’s need for reciprocity (‘connect with me’); maintaining their identity (‘see who I am’); and sharing decision-making (‘include me’). There is now a substantial body of evidence from which to conclude that older people place great importance on the relational aspects of their care and, when this falls short, its absence is felt most acutely.

Perhaps due to the nature of the work they do, nurses have often been targeted as both the source of the problem and the solution to concerns about loss of dignity for patients in hospital [3]. However, within the NHS, Band 2 and Band 3 support workers, also known as healthcare assistants (HCAs), have become an increasingly important section of the workforce, particularly in relation to older people, with observational data suggesting that the proportion of their time delivering direct and indirect patient care is approximately 60 %, nearly twice that of registered nurses [15]. Demographically, HCAs tend to differ from registered nurses, more closely resembling the ethnic diversity of the patient population they serve [16] and likely to be a more ‘static’ part of the workforce. The problems of invisibility, marginalisation and subordination of the ‘caring’ work of nurses [17] are likely to be replicated in HCAs whose work often gets little recognition, even from other staff groups [18].

Although investments in staffing and work environments are pre-requisites for high-quality care [12, 19], historically HCAs have been viewed as the ‘untrained workforce’ leading to an assumption that they are without training needs [20]. HCAs and nurses are largely in favour of more formal training for HCAs, although a blurring of role boundaries is of concern to both staff groups [21]. Among employing organisations there is a lack of consistency in HCA training and how HCAs interface with registered nurses [22]. Moreover, it appears that HCAs often lack confidence in pursuing the few training opportunities available to them [16, 18]. Ethnographic observational data of HCAs working in dementia wards suggest that support in carrying out such a challenging role is drawn from the formation of close-knit groups of HCAs who are sometimes disconnected from the wider ward team [23], resulting in HCAs feeling alienated from the organisation in which they work [24].

Training of HCAs has hitherto been ad hoc, variable, and marked by a tendency to focus on tasks and competencies, with little attention paid to relational care. The importance of using principles of instructional (pedagogical) design [25] to develop educational and training interventions is rarely considered. This is essential to ensure that training builds on existing knowledge and values, harnesses intrinsic motivation, and actively engages learners.

To date, evaluations of training interventions for HCAs have been few, are typically lacking any comparative element (e.g. [26]), and are often small-scale. In terms of Kirkpatrick’s four-level training evaluation model [27], studies of HCA training rarely measure outcomes other than those that are first-level and ‘reactive’ (for example trainee satisfaction) and greater efforts should be made to see how training translates into fourth-level benefits or ‘results’ (for example patient outcomes). This study will pilot ‘Older People’s Shoes’, a newly developed evidence-based HCA training package designed to improve the quality of relational care of older people and investigate the feasibility of testing its effectiveness in a definitive randomised controlled trial.

### Aims of the study

The aims of the study are to assess the feasibility of a cluster randomised controlled trial to compare the performance of an HCA training package in relational care against current training in improving the care of older patients in acute NHS settings, and to explore optimal methods for cost-benefit analysis for a definitive study.

Important parameters that are needed to inform the feasibility of a definitive trial (and if feasible, then the design of such a trial) [28] will be assessed:The acceptability of the intervention to trainers and HCA trainees.The willingness of ward managers, HCAs and older patients to participate in a cluster randomised controlled trial.The willingness of ward managers for wards to be randomly allocated.The level of non-response and item non-response to outcomes at the level of ward, HCA and patient.The acceptability of outcome measures to participants.The ability to monitor levels of resource-use and quality of life data.The variability within and between ward, HCA and patient outcomes.The appropriateness of ward as the unit of randomisation.

## Methods/Design

### Trial design

A pilot cluster randomised controlled trial will be conducted to compare an ‘HCA training package in relational care’ with ‘HCA training as usual’. Clusters are wards within three acute NHS Hospital Trusts in England with outcomes observed at the level of ward, HCA and patient (Fig. 1).

**Fig. 1 Fig1:**
[figure not shown]
Can Healthcare Assistants Training improve the relational care of older people? (CHAT) pilot cluster randomised controlled trial design

### Eligibility criteria

#### Wards

General medical, stroke or wards for the care of older people are eligible to enter the trial. Specialist dementia wards and medical admissions units are excluded.

#### Healthcare assistants

HCAs employed full time or part time within enrolled wards are eligible to enter the trial. Those employed as bank staff and not part of the named staff on the ward roster are ineligible.

#### Patients

Patients will be eligible if they are aged 70 years or over and discharged from an inpatient stay on an enrolled ward, during either the 4-week period prior to randomisation (baseline) or during weeks 9 to 12 post-randomisation (follow-up). Patients transferred to another ward or hospital prior to discharge or considered by the nurse-in-charge not to have mental capacity (according to the Mental Capacity Act 2005) or to be in the final stages of a terminal illness are excluded.

### Recruitment

#### Wards

The ward manager provides permission for ward participation. Recruitment of wards will cease once permission is given by ward managers of 4 eligible wards from each of 3 acute NHS Hospital Trusts (*n* = 12 wards in total).

#### Healthcare assistants

Within each of the enrolled wards all HCAs will be invited to take part in the study by a researcher employed on the grant. At a number of ward-based meetings during the 4-week baseline period HCAs are given information about the study. Informed consent will be obtained from all HCA participants.

#### Patients

The initial approach of patients will be made on the enrolled ward a few days prior to their discharge. Older patients (aged 70 years or over) receiving inpatient care from the enrolled wards in the 4-week baseline period and the 4-week follow-up period will be identified by a hospital-based research nurse in consultation with ward managers. Informed consent will be obtained from all patient participants. The research nurse will approach each of the patients meeting eligibility criteria, explain the study, and provide the patient with a participant information sheet. If they agree to receive a questionnaire after discharge from hospital, the research nurse will ask them to sign a consent form.

### Baseline measures

#### Wards

To assess quality of interactions within a ward the Quality of Interaction Schedule (QUIS) observation tool is used by a trained observer at each hospital [29]. QUIS is an observational strategy in which interactions between patients and care staff are coded as positive social (interactions involving conversation and companionship), positive care (interactions during the appropriate delivery of care), neutral (brief and indifferent interactions), negative protective (keeping safe without explanation or reassurance) or negative restrictive (opposing or resisting patients’ freedom of action without good reason). Ward observations take place over the 4-week period prior to randomisation. Each observation is conducted over a 50-minute period by 1 observer. The interactions observed are those that involve a patient and at least one HCA. Eight observations per ward will be conducted during the baseline period. Observations take place during mornings, mealtimes and visiting periods. On four occasions at each hospital, observations will be conducted in pairs to assess inter-rater reliability.

#### Healthcare assistants

At baseline, HCAs receive a self-completion questionnaire containing the Assessment of Work Environment Schedule (AWES), [30, 31] the Toronto Empathy Questionnaire (TEQ) [32], and the Age Group Evaluation and Description (AGED) inventory [33]. The 34-item AWES measures HCA perception of the support provided in the work environment. The TEQ conceptualises empathy as an emotional process and contains 16-items, each a statement about empathetic responses to specific situations with which the HCA respondent is asked to rate on a 5-point scale their agreement. The AGED inventory measures the extent to which stereotypes about ageing are held by the respondent. It includes 28 semantic differentials relating to a specific age group (70 years and over) using a 7-point Likert scale.

#### Patients

At 2 weeks after discharge from hospital, patients who have consented to participate receive a questionnaire and pre-paid addressed envelope. To assess the relational aspects of care experienced by patients, the Patient Evaluation of Emotional Care during Hospitalisation (PEECH) [34, 35] is used. The PEECH was developed for acute hospital settings and contains 23 items and 4 subscales of levels of security, knowing, personal value and connection. Patients are asked to rate the extent (on a four-point scale) to which hospital staff responded or behaved in particular situations. To assess quality of life, the self-report version of the European Quality of Life 5 Dimensions 5 Levels (EQ-5D-5L) [36] is used.

### Allocation for trial interventions

Stratified by NHS Hospital Trust, 12 wards will be randomly allocated by the Norwich Clinical Trials Unit. Each ward has an equal chance of receiving either training for HCAs in relational care or training as usual. Random allocation is generated via computer-written code. To conceal allocation from those responsible for recruitment, randomisation takes place immediately after baseline measures are completed and 4 weeks ahead of the start of the intervention (set-up period) to allow appropriate arrangements including HCA cover.

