### Outcomes

Outcomes at all levels (ward, HCA and patient) will be observed during weeks 9 to 12 after randomisation. The primary outcome is at the level of patient (PEECH score).

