#### Patients

Patients due to be discharged from enrolled wards between weeks 9 and 12 post-randomisation will be approached, recruited and administered questionnaires in an identical way to that used in the baseline period.

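### Randomising after baseline conceals allocation for wards, HCAs and baseline patients, but not for the follow-up patients who supply the primary PEECH outcome

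*Protocol article*

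**What the plan says.** All references are to the protocol article.

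- **Allocation for trial interventions.** The unit is the ward: "Stratified by NHS Hospital Trust, 12 wards will be randomly allocated by the Norwich Clinical Trials Unit". One mechanism of concealment is given: "To conceal allocation from those responsible for recruitment, randomisation takes place immediately after baseline measures are completed". A four-week set-up period follows, partly so that cover for HCAs can be arranged.
- **Outcomes.** The primary outcome is the patient-level PEECH score. On timing: "Outcomes at all levels (ward, HCA and patient) will be observed during weeks 9 to 12 after randomisation".
- **Outcomes, Patients.** The follow-up sample is recruited afresh, by the baseline methods: "Patients due to be discharged from enrolled wards between weeks 9 and 12 post-randomisation will be approached, recruited and administered questionnaires".
- **Recruitment, Patients.** Patients "will be identified by a hospital-based research nurse in consultation with ward managers". The same paragraph says that the research nurse approaches each patient who meets the criteria.
- **Eligibility criteria, Patients.** Among those excluded are patients "considered by the nurse-in-charge not to have mental capacity" or, on the same person's judgement, in the last stages of a terminal illness. Baseline patients are those discharged in the four weeks before randomisation.
- **Baseline measures, Patients.** "At 2 weeks after discharge from hospital, patients who have consented to participate receive a questionnaire", which contains PEECH.

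**The concern.** In a cluster trial, randomising the wards does not protect against selection of the individuals who are later measured. If patients are identified after allocation, with input from staff who know it, the two arms can end up with different kinds of patients although the wards were allocated at random. The Allocation section reads as if this problem were solved for recruitment in general.

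Two things are at stake. The first is the between-arm PEECH difference, for which the Statistical analysis section plans confidence intervals. The second is the set of feasibility parameters under Aims of the study: patients' willingness to take part, non-response, and variability within and between wards. All of these depend on who is identified and approached. The pilot is also meant to judge whether the ward is a suitable unit of randomisation. A statement that concealment is already secured hides a question the pilot is well placed to answer.

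The analysis cannot repair this. The patient-level intention-to-treat set consists of the patients recruited, so it takes any differential recruitment as given. Follow-up patients are a separate sample, so none has a PEECH score of their own from before randomisation. The optional adjustment for baseline factors would deal only with measured differences.

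**Working it through.** No sample size or power figure is involved, so the check is a timeline with randomisation at day 0.

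**1. Recruitment of the primary-outcome patients**

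- Training (Intervention): weeks 5 to 8, days 28 to 55.
- Follow-up discharges (Eligibility criteria; Outcomes): weeks 9 to 12, days 56 to 83.
- Approach (Recruitment): shortly before discharge. If that means at most 7 days (my assumption), the earliest approach is day 56 − 7 = 49.
- Expected follow-up patients (Sample size): 100.
- Follow-up patients recruited before allocation: 0 of about 100.

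The stated mechanism therefore covers none of them. For the other groups it does hold: ward managers' permission, HCA consent and consent of baseline patients all come before day 0.

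**2. Where discretion remains after allocation**

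- Age 70 or over and discharge from an enrolled ward within the window are objective criteria.
- The capacity and terminal-illness exclusions are judgements made on the ward.
- Ward managers are consulted on identification. That they know the allocation is inferred from three facts: the ward is the randomised unit, its manager gave permission to take part, and cover must be arranged while HCAs attend two days of training.

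**3. Timing of PEECH (minor)**

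- Baseline discharges: days −28 to −1. Posting at discharge + 14: days −14 to 13.
- Posted on or after day 0: discharges on days −14 to −1, that is 14/28 = 50%, about 50 of 100 if discharges are evenly spread (assumption).
- Not yet returned by day 0, by assumed return lag: 0 days, 14/28 = 50%; 7 days, 21/28 = 75%; 14 days, 28/28 = 100%.
- Follow-up posting: days 56 + 14 = 70 to 83 + 14 = 97, that is weeks 11 to 14. Posted after week 12: 14/28 = 50%.

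This does not fit the Allocation section (baseline measures complete at randomisation), the Outcomes section (outcomes observed in weeks 9 to 12) or the Sample size section (questionnaires received within each four-week period).

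**The case against.** The strongest reply is that the research nurse is to approach every eligible patient. That is not sampling from names supplied by the ward. A reader might infer that ward managers choose the patients; the article says only that they are consulted. This stands, and it reduces the concern to the judged exclusions and to imperfect execution on a busy ward.

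A reader might also take it as documented that ward managers, or the research nurse, know the allocation. It is not. For ward managers it is a strong inference. For the research nurse the article is silent, and a condensed article's silence is not an error.

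The concealment sentence can also be read narrowly, as covering only recruitment up to baseline. On that reading it is true but incomplete, because it refers without limit to those responsible for recruitment, and the same recruitment process is repeated in weeks 9 to 12.

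Finally, this is a pilot, not powered for superiority, and no efficacy claim hangs on PEECH. That lowers the stakes for the treatment difference. It does not lower them for the recruitment and response rates, which are the pilot's product.

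On baseline timing, the late forms describe stays that ended before randomisation, and the stated PEECH model contains only intervention and ward. A reader might infer that baseline PEECH is contaminated by the intervention; the article does not support that.

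**Conclusion.** The concern holds in a limited form. The stated concealment protects wards, HCAs and baseline patients. It covers none of the roughly 100 expected follow-up patients, all of whom are identified and consented after allocation, with input from ward staff who very probably know it. This leaves a route for differential identification that could distort both the PEECH difference and the feasibility rates.

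The size and direction of any bias cannot be derived from the article. It would be wrong to conclude that the PEECH comparison is biased; what is shown is that the named protection does not extend to it. The conclusion rests on the article's own timeline, plus the inference about ward managers.

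The timing mismatch is real but is a matter of wording. The figure of about half assumes evenly spread discharges.

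**What to change.** 1. Limit the concealment statement to wards, HCAs and baseline patients, and say plainly that follow-up patients are recruited after allocation.
2. In weeks 9 to 12, have the existing research nurse identify all patients aged 70 or over consecutively from the ward discharge list. Where possible, do not tell the nurse the ward's allocation.
3. Report the numbers eligible, excluded (with reason), approached, consented and returned, by arm and period, and compare age and length of stay.
4. Acknowledge the residual risk of selection bias.
5. Define the baseline and follow-up patient samples by discharge date, and reconcile the Eligibility criteria, Baseline measures, Allocation, Outcomes and Sample size sections on when PEECH is sent and received.

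The cost is small: instructions to staff already in post, a record of patient flow, and corrected wording. The downside is that masking on the ward will be imperfect. Randomisation should not be delayed until the last baseline form is due: that would move set-up, training and follow-up by at least two weeks for a minor gain. If follow-up recruitment is already over, items 1, 4 and 5 still apply, as does item 3 as far as records allow.
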